### Statistical Analysis

Relationships between Total Mayo Scores and Sum Endoscopic Mayo Scores will be assessed using a *t*-test. Furthermore, the correlation between the relative abundance of Bacteroidetes species using a Pearson's correlation coefficient will be evaluated. Differences will be considered significant at *P* < 0.05.

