**Methods and Analysis:**

This trial is a double-blinded, randomized, placebo-controlled, parallel assignment trial. Patients with UC and fecal donation candidates will undergo strict screening before being involved in the trial. Eligible patients are randomly divided into two groups: one group will drink one bottle of alginate twice a day for 8 consecutive weeks after A-FMT, while the other group will take a placebo instead of the alginate drink. The primary endpoints are the changes in the Total Mayo Score at 8 weeks after study initiation and A-FMT from baseline. The secondary endpoint is the comparison of clinical features, microbiota, and metabolomic analysis before and after 8 weeks of study food intake. Changes at 6, 12, 18, and 24 months after A-FMT will be assessed. Finally, a subpopulation analysis of the relationship between patients and donors is an exploratory endpoint.

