### Outcomes

The primary endpoint is to compare the changes in the Total Mayo Score at 8 weeks after study initiation and A-FMT from baseline between alginate intake group and placebo intake group. The secondary endpoints are the comparison of the following items at 8 weeks after study initiation and A-FMT from baseline:

The change in the Sum Endoscopic Mayo Score.Analysis of intestinal microbiota by 16S rRNA gene amplicon sequencing and whole-genome sequencing.Metabolomic analysis: In addition to SCFAs in stool samples, the amount of lipids, free fatty acids, bile acids, and other clinical markers will also be measured by liquid chromatography tandem mass spectrometry (35).

We will also do same analysis as (1), (2), and (3) at 6, 12, 18, and 24 months after 8 weeks post-study initiation.

Subpopulation analysis of the relationship between patients and donors is considered an exploratory endpoint.

Clinical features will be judged by the Total Mayo Score, and the mucosal appearance of the Mayo Score will be evaluated by endoscopy. To evaluate the overall status of the intestine, endoscopic findings will be evaluated using the Sum Endoscopic Mayo Score, which refers to the sum of the scores of the seven segments (appendicular region, cecum, ascending colon, transverse colon, descending colon, sigmoid colon, and rectum). Intestinal microbial analysis will assess changes in composition and diversity. Metabolomic analysis will evaluate the metabolites of microbiota and elucidate the mechanism of action of alginate in the treatment of UC.

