### Sample Size Estimation

In our previous clinical trials (15), ~40 eligible patients with UC were collected in 1 year. Therefore, conservative estimates predict that 60 patients can be collected over 3 years. Eligible patients with UC will be randomized and assigned to two groups with a ratio of 1:1 in a double-blinded fashion. The estimated difference between each group in the Total Mayo Score as the primary endpoint from baseline is −2, and the standard deviation of each group is estimated to be ~2.5. If a two-sample *t*-test is used to test the difference between groups, a power analysis predicts that statistical significance with a power of ~86.1% can be reached.

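### The Statistical Analysis section gives a t-test to the relationship between two scores and names no arms, and the secondary endpoints are left open to a before-after reading

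*Protocol article*

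**What the plan says.** The Statistical Analysis section of the protocol article has three sentences.

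- On the clinical scores: "Relationships between Total Mayo Scores and Sum Endoscopic Mayo Scores will be assessed using a" t-test.
- On the microbiota: "the correlation between the relative abundance of Bacteroidetes species using a Pearson's correlation coefficient will be evaluated". No second variable is named.
- On significance: "Differences will be considered significant at *P* < 0.05".

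None of them mentions alginate, placebo or change from baseline.

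Other sections bear on the same analyses.

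- **Outcomes, primary endpoint:** the change in Total Mayo Score is compared "from baseline between alginate intake group and placebo intake group".
- **Sample Size Estimation:** "The estimated difference between each group in the Total Mayo Score as the primary endpoint from baseline is −2". The SD is about 2.5 per group, allocation is 1:1, and a two-sample t-test between groups is said to give about 86.1% power. Study Design and Patients gives 60 patients in total.
- **Outcomes, secondary endpoints:** "The secondary endpoints are the comparison of the following items at 8 weeks after study initiation and A-FMT from baseline". The arms are not repeated. The same analyses are then to be done at 6, 12, 18 and 24 months.
- **Abstract, Methods and Analysis:** "The secondary endpoint is the comparison of clinical features, microbiota, and metabolomic analysis before and after 8 weeks of study food intake".
- **Discussion:** the hypotheses are between arms. Microbial diversity and the Bacteroidetes share are expected to be higher with alginate than with placebo, and the clinical results better.

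**The concern.** There are two linked problems.

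First, the sentence on the two Mayo scores pairs a method with a question that it cannot answer. A t-test asks whether two means differ; a relationship between two variables calls for a correlation or a regression. Taken literally, the sentence sets one scale against another. The Sum Endoscopic Mayo Score adds up seven bowel segments, and the Total Mayo Score is a separate clinical index. A difference between their means has no interpretation and says nothing about alginate. The section that should carry out the randomised comparison does not state it.

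Second, the abstract words the secondary endpoints as before versus after, and Outcomes does not settle the matter. All patients have the antibiotic course and FMT before randomisation. A change within one arm over the following 8 weeks therefore mixes the effect of A-FMT, regression to the mean in patients selected for active disease, and any effect of alginate. If the secondary endpoints were analysed that way, significant improvements in endoscopic, microbial or metabolic measures could be credited to a drink that did nothing. The later time points repeat the same analyses and inherit the ambiguity.

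**Working it through.** **1. Reproduce the plan's own power.** Inputs from Sample Size Estimation and Study Design and Patients: difference 2, SD 2.5, 60 patients at 1:1, so n = 30 per arm. Alpha is 0.05 from Statistical Analysis, taken as two-sided because the side is not stated.

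- Noncentrality = 2 / (2.5 × √(2/30)) = 2 / 0.6455 = 3.10, with 58 degrees of freedom.
- Power from the noncentral t distribution = 86.14%, against about 86.1% stated.
- The normal approximation gives 87.25%. A one-sided 0.05 test gives 92.7% under the same approximation, which does not match.

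The trial was thus sized for a two-sided, between-arm t-test on the change in Total Mayo Score.

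**2. Set the statements side by side.**

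| Place | What is compared | Arms named? |
|---|---|---|
| Outcomes, primary | Change in Total Mayo Score | Yes |
| Sample Size Estimation | Same, two-sample t-test | Yes (between groups) |
| Statistical Analysis | Total Mayo and Sum Endoscopic Mayo, t-test for a relationship | No |
| Outcomes, secondary | Listed items at 8 weeks from baseline | No |
| Abstract, secondary | Before and after 8 weeks of study food | No |
| Discussion | Microbiota and clinical results, alginate against placebo | Yes |

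The primary comparison is consistent in two places and missing from the analysis section. The secondary comparison is between arms in the Discussion, before-after in the abstract, and open in Outcomes.

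**3. Why a literal t-test of the two scores is uninformative.** Table 4 gives baseline values of 7.12 ± 1.9 (Total Mayo) and 6.5 ± 4.2 (Sum Endoscopic Mayo). The means lie 0.62 apart (7.12 − 6.5), but on different scales. Whether that gap is significant tells us neither whether the scores move together nor whether alginate works.

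**4. Illustration of a before-after reading.** Assume an inert drink, n = 30 in one arm, SD of change 2.5, two-sided alpha 0.05 and a mean improvement c from A-FMT alone. The values of c are assumptions. The SD is the plan's Total Mayo figure, borrowed because the article gives no SD of change for any secondary endpoint.

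- Standard error of the mean change = 2.5 / √30 = 0.456; noncentrality = c / 0.456; 29 degrees of freedom.

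| Assumed c | Noncentrality | Chance of a significant before-after test |
|---|---|---|
| 0 | 0 | 5% |
| 1 | 2.19 | 56% |
| 1.5 | 3.29 | 89% |
| 2 | 4.38 | 99% |

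A between-arm test with an inert drink is significant 5% of the time whatever c is, because c cancels. The Introduction reports 43.8% clinical remission four weeks after A-FMT without alginate. That makes some background improvement plausible, but it is a remission rate and cannot be converted into c.

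**The case against.** The strongest reply is that the article already isolates the alginate effect where it matters most. Outcomes compares the primary endpoint between the two groups, and Sample Size Estimation names the between-group t-test and powers it correctly. This stands. A reader might infer from the Statistical Analysis section alone that the trial has no analysis of alginate against placebo; the other two sections rule that out for the primary endpoint.

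It can also be said that the secondary sentence under Outcomes follows directly on the between-group definition and reuses its timing phrase, so the arms may simply carry over, and that the abstract leaves the arms out of the primary endpoint too. This is a fair reading, and the Discussion's hypotheses support it. A reader might infer that the randomised control will be unused for every secondary endpoint; the documents do not establish that. They leave it open, and the abstract's explicit before-after wording points the other way.

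Third, the word paired appears nowhere, and the sentence on the two scores may be a clumsy way of saying that each will be t-tested between groups. That is quite likely the intent, but it is not what the sentence says.

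Finally, the illustration uses the SD of the one endpoint that is explicitly compared between arms, with assumed improvements. This is correct, and the figures should be read only as an illustration.

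**Conclusion.** The concern holds in a limited form. The sentence on the two Mayo scores is invalid as written: it gives the wrong method for a relationship, treats two different scales together and names no arms. It is inconsistent with the primary endpoint under Outcomes and with the two-sample t-test behind the 86.14% power. The abstract words the secondary endpoints as before versus after, and Outcomes does not correct this by naming the arms.

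The primary endpoint is not affected. For the secondary endpoints, a within-arm analysis would not isolate alginate, because A-FMT is common to all patients. The 56% and 99% figures show how misleading such an analysis could be, but only under the assumed 1-point and 2-point improvements, 30 patients and an SD of 2.5. No such figure can be derived for the actual secondary endpoints from this article. Further modelling detail may sit in an analysis plan that is not shown, and its absence here is not counted against the trial.

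**What to change.** Replace the sentence on the two Mayo scores in Statistical Analysis with:

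> The Total Mayo Score (primary) and the Sum Endoscopic Mayo Score (secondary) at week 8 will each be compared between the alginate and placebo groups, adjusted for the baseline score. Any association between the two scores will be described with a correlation coefficient.

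Baseline adjustment is the recommended form. The two-sample t-test on change already named under Sample Size Estimation would also remove the inconsistency.

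In the abstract and under Outcomes, state that the secondary endpoints are between-arm comparisons of change, at 8 weeks and at the later time points, and that within-arm changes are descriptive only. While editing, name the second variable of the Pearson correlation.

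The cost is wording only, with no change to sample size, visits or data collection. The article reports 33 of 60 patients enrolled on December 8, 2021 and allocation concealed until the trial is finished, so the change fits before unblinding. If unblinding has already happened, the revised analysis should be dated and reported as such.

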## Discussion

FMT is a well-established treatment regimen for recurrent *Clostridium difficile* infection (CDI). Clinical practice guidelines clearly state that FMT can be used as a treatment option for CDI (36, 37). However, using FMT for UC treatment remains in the clinical trial stage. Since 2014, we have been committed to studying how to enhance the therapeutic effect and operational feasibility of FMT on UC in clinical trials. The proposed A-FMT method has a significant effect on the treatment of UC in our previous studies. We hope to combine acceptable and convenient post-treatment methods based on A-FMT to further enhance the effect and prolong the remission period, including alginate supplements.

Alginate has the potential to increase the relative abundance of some beneficial Bacteroidetes members, resulting in an improved intestinal environment (38–40). Therefore, we hypothesize that the diversity of microbiota and the proportion of Bacteroidetes in the group treated with A-FMT combined with alginate will be higher than that in the placebo group. An increased number of Bacteroidetes species can suppress the inflammatory response through zwitterionic capsular polysaccharides, which are bacterial products that modulate T cells to secrete the anti-inflammatory interleukin-10 (41). It has also been reported that alginate can be fermented by specific bacteria in feces, such as *Bacteroides ovatus, Bacteroides xylanisolvens*, and *Bacteroides theaiotaomicron* (30, 42), which can induce colonic regulatory T cells and promote anti-inflammatory effects (28, 43). Therefore, we believe that oral supplementation of alginate with exogenous sources can contribute to the intestinal anti-inflammatory response. Furthermore, we expect that the group treated with A-FMT combined with alginate will demonstrate better results in terms of clinical features and microbial analysis, and will retain its advantage over the placebo arm after 2 years' follow-up. The metabolites produced by microbiota can shape the colonic environment through a variety of activities, such as participating in signaling, immune system modulation, and antibiotic activity (44–46). However, it is not fully known how specific microbes and the small molecules they modulate interact to cause or control the inflammatory response. Therefore, in our study, a wide range of metabolomic analyses other than SCFAs will be included in the study.

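### The plan fixes Pearson's coefficient on raw Bacteroidetes proportions, names no second variable, and sets one P < 0.05 rule not limited to the primary endpoint although sequencing and metabolomic endpoints are planned at five times

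*Protocol article*

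**What the plan says.** The Statistical Analysis section of the protocol article has three sentences. The first assigns a t-test to the Mayo scores. The second says that "the correlation between the relative abundance of Bacteroidetes species using a Pearson's correlation coefficient will be evaluated"; it does not say with what the abundance is to be correlated. The third is the only significance rule in the article: "Differences will be considered significant at *P* < 0.05". It follows the microbiota sentence directly and is not confined to any endpoint.

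The Outcomes section lists among the secondary endpoints "Analysis of intestinal microbiota by 16S rRNA gene amplicon sequencing and whole-genome sequencing". For metabolomics it says that, besides short-chain fatty acids, "the amount of lipids, free fatty acids, bile acids, and other clinical markers will also be measured by liquid chromatography tandem mass spectrometry". It then adds "We will also do same analysis as (1), (2), and (3) at 6, 12, 18, and 24 months", which makes five time points with week 8. The Discussion promises that "a wide range of metabolomic analyses other than SCFAs will be included in the study". The article does not give the number of taxa or metabolites.

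**The concern.** There are three problems, all in what the text states.

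- **Undefined correlation.** With one side missing, the sentence can mean species against each other, or species against a clinical score. The two readings have different statistical weaknesses, and an analyst could choose between them after seeing the data.
- **Unsuitable scale.** Relative abundances are bounded, usually skewed, often zero, and sum to a constant over the community. Pearson's coefficient on the raw values is sensitive to all of this.
- **One threshold for everything.** A 0.05 rule suits one primary test. Over a panel of taxa and metabolites, some features will be called significant even if alginate does nothing.

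The microbiota and metabolite data carry the mechanistic part of the trial. The Introduction makes greater microbiota diversity part of the aim. The Discussion predicts higher diversity and a higher Bacteroidetes proportion with alginate. The Outcomes section expects metabolomics to explain how alginate works.

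**Working it through.** **Inputs from the article.** 60 patients (Study Design and Patients), allocated 1:1, so 30 per arm; difference 2, SD 2.5, power about 86.1% (Sample Size Estimation); threshold 0.05 (Statistical Analysis); five time points (Outcomes). **Assumed, because not given:** the number of features m, the skew and zeros in the abundances, the true correlation, and the number of parts in the composition.

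**1. The plan's own figure.** Noncentrality = 2 / (2.5 × √(1/30 + 1/30)) = 2 / 0.6455 = 3.098. With 58 degrees of freedom and two-sided 0.05, power is 86.14%. The stated 86.1% reproduces and is not in question.

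**2. Flat threshold.** With m true nulls, the expected number of false positives is 0.05 × m, whether or not the tests are independent. The chance of at least one is 1 − 0.95^m if they are independent.

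| m (assumed) | Expected false positives | Chance of at least one |
|---|---|---|
| 20 | 1.0 | 64.2% |
| 50 | 2.5 | 92.3% |
| 100 | 5.0 | 99.4% |

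These are per time point. Testing the same panel at five times multiplies the expected count by five, to 5 at m = 20 and 25 at m = 100.

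**3. If abundance is correlated with a Mayo score.** Simulation at n = 60: log-normal abundance, a normally distributed outcome, latent correlation 0.4, log-SD 1 to 2, from no zeros to half zeros. Power is about 48-76% for raw Pearson and 79-87% for Spearman. With latent correlation 0.35 and no zeros it is 62% against 74% at log-SD 1, and 38% against 73% at log-SD 2. With no true association, raw Pearson rejected in 4.9-5.5% of runs. The harm on this reading is lost sensitivity, not false positives.

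**4. If species are correlated with each other.** Truly independent log-normal taxa were converted to proportions, n = 60. Log-SD is 1 in the even rows and 1.5 in the dominant rows, which give the correlation of the dominant taxon with another.

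| Composition | Mean Pearson r | Pearson rejects | Spearman rejects |
|---|---|---|---|
| 3 even parts | −0.50 | 99% | 95% |
| 5 even parts | −0.24 | 48% | 28% |
| 10 even parts | −0.10 | 5% | 7% |
| 20 even parts | −0.05 | 2% | 6% |
| 50 even parts | −0.02 | 4% | 6% |
| 10 parts, one dominant | −0.32 | 80% | 85% |
| 20 parts, one dominant | −0.21 | 32% | 49% |

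The bias is large with few parts or a dominant taxon and small with many even parts. Spearman does not remove it.

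**5. What a log-ratio transform does.** For independent taxa with equal log-variance, centred-log-ratio (CLR) values have pairwise correlation −1/(K − 1), whatever the mean abundances. With 10 parts this is −1/9 = −0.11, against −0.32 for raw proportions with a dominant taxon. With 3 parts it is still −1/2 = −0.50. CLR therefore removes the dominance effect, but should be computed over the whole sequenced community and not over a handful of species.

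**The case against.** The best defence is that a journal article condenses the full plan. Handling of multiplicity in omics data is commonly left to a statistical analysis plan, which is not shown, and a 0.05 level is compatible with FDR-adjusted P values. That stands: the absence of an FDR step is not itself a finding. The point rests on what is written, namely a named coefficient on a named scale, a missing second variable, and an unqualified threshold.

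Several stronger readings are tempting, and the article does not support them:

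- *Pearson is fixed for all sequencing and metabolomic endpoints.* It is tied only to Bacteroidetes species. No test is named for metabolites, diversity or other taxa.
- *Species correlations are negative by construction.* A constant sum makes each part's covariances with the others negative in total, not pair by pair. Bacteroidetes species are also only a subset of the community and need not sum to a constant among themselves. In a simulation with 50-100 parts, mean r was −0.02 to +0.03, with 3-8% rejected.
- *Raw Pearson against a Mayo score produces false positives.* It does not, as step 3 shows. This is arguably the intended reading, since the Introduction links Bacteroidetes composition to clinical response and severity.
- *Dozens of false positives will undermine the stated hypotheses.* The count depends on an unstated m. The two hypotheses in the Discussion concern diversity and the Bacteroidetes proportion, which are few measures and not a large panel.

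**Conclusion.** The concern holds as a correction to the secondary analyses. That the second variable is missing and the threshold is unqualified can be read from the text without any assumption.

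The sizes rest on assumptions. The cost of raw Pearson against a Mayo score is roughly 10 to 40 percentage points of power, depending on skew, zeros and the true correlation. The closure bias between species ranges from severe to negligible with the number and evenness of parts. The flat rule yields 1 expected false positive per time point for every 20 null features. The primary comparison of Total Mayo Score change, and its power, are untouched.

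**What to change.** - Name the second variable: change in Total Mayo Score and in Sum Endoscopic Mayo Score. Week 8 is the natural time, since Table 3 marks no endoscopy after it.
- Use Spearman's coefficient for abundance against those scores.
- For any species-against-species correlation, use log-ratio values such as CLR, computed over the whole community. Spearman alone is not enough there.
- Keep unadjusted P < 0.05 for the primary endpoint and for one named microbiota measure, for example the Bacteroidetes proportion at week 8.
- For all other features, control the Benjamini-Hochberg FDR at 5% within each omics layer and time point. This needs no feature count fixed in advance.

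The cost is a few sentences of wording and minor programming. It should be done before unblinding; the Randomization section keeps allocation concealed until the trial has finished. The downside is that fewer individual taxa and metabolites will be called significant. Control is also per family: 3 layers × 5 times = 15 families, so if nothing is real about 15 × 0.05 = 0.75 families would still show a finding. The report should state this.
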